## Abstract

**Background:**

Ankle sprain is a common musculoskeletal injury. In Korean medicine, blood stasis is thought to be the main cause of pain and swelling in patients with ankle sprain. *Dangguixu-san* (DS), a herbal extract, is widely used in Korean medicine for the treatment of traumatic ecchymosis and pain by promoting blood circulation and relieving blood stasis. However, the effects of DS on ankle sprain have not been evaluated in a randomized clinical trial. Here, we describe the protocol for a randomized controlled trial that will evaluate the efficacy and safety of DS for the treatment of ankle sprain.

**Methods/design:**

In this randomized, double-blinded, placebo-controlled, parallel-arm clinical trial with a 1:1 allocation ratio, participants (*n* = 48) with acute lateral ankle sprain (ALAS) that occurred within 72 h before enrollment will be randomly assigned to a DS (*n* = 24) or a placebo (*n* = 24) group. Both groups will receive acupuncture treatment once a day for 5 days a week (excluding Saturday and Sunday) and the trial medication (DS/placebo capsule) three times a day for seven consecutive days. The primary outcome measure will be pain relief evaluated using a Visual Analog Scale (VAS). Secondary outcome measures will include Foot and Ankle Outcome Scores (FAOS), edema, European Quality of Life Five-Dimension-Five-Level Scale (EQ-5D-5 L) scores, and the number of recurrent ankle sprains. VAS, FAOS, edema, and EQ-5D-5 L scores will be recorded before, at the end of, and at 4 weeks after treatment completion. EQ-5D-5 L scores will be additionally recorded at 26 weeks after treatment completion. The number of recurrent ankle sprains will be recorded at 4, 8, 12, and 26 weeks after treatment completion.

**Discussion:**

This study is expected to provide evidence regarding the efficacy, safety, and usefulness of DS for the treatment of ALAS.

**Trial registration:**

cris.nih.go.kr, registration number: KCT 0002374. Registered on 11 July, 2017 and approved by the Ministry of Food and Drug Safety (registration number, 31244).

**Electronic supplementary material:**

The online version of this article (10.1186/s13063-018-2571-1) contains supplementary material, which is available to authorized users.

## Background

Ankle sprain is one of the more common musculoskeletal injuries and is associated with a high prevalence of persistent problems that lead to an increased burden of chronic health issues in the community [1–5]. The annual incidence rate of ankle sprain ranges from 2.15 per 1000 individuals in the USA (resulting in a cumulative healthcare cost of US$4.5 billion per annum) [1, 2] to 5.3–7.0 per 1000 individuals in Europe [3, 6]. Ankle sprain is commonly considered a benign injury that resolves quickly [7]. However, at least a third of individuals who develop an acute ankle sprain develop chronic ankle instability (CAI) [8–10], which is characterized by residual symptoms, including a feeling of “giving way” and instability, recurrent ankle sprain, and functional loss after acute ankle sprain [11]. CAI not only limits physical activity but also leads to articular degeneration of the ankle joint and an increased risk of osteoarthritis [12]. The three major types of treatment for ankle sprain are surgical treatment, conservative treatment involving immobilization with a plaster cast or splint, and functional conservative treatment with a tape or a semi-rigid or lace-up brace [13].

Blood stasis is an important pathological concept in traditional East Asian medicine (TEAM) since it was first documented in *Huangdi’s Inner Classic*. Generally, blood stasis is a significant pathological product of blood stagnation [14, 15]. Blood stasis occurring within the body is termed blood stasis syndrome (BSS), which is characterized by symptoms such as pain in a fixed position, nyctalgia, dark-purple coloring of the tongue and face, infraorbital darkness, sublingual varicosis, blood spots under the skin or tongue, and an astringent pulse [16]. According to TEAM, many diseases, including ischemic heart disease, cerebrovascular events, diabetes mellitus, chronic gastritis, chronic renal failure, chronic hepatitis, trauma, and dysmenorrhea, could be related to BSS [17, 18]. This phenomenon is termed *EoHyeol* in Korean, *Yu Xue* in Chinese, and *Oketsu* in Japanese [19].

In Korean medicine, because it is considered that pain and swelling associated with ankle sprain could be caused by blood stasis, activation of blood circulation is the main treatment principle for ankle sprain [20, 21]. In addition to conventional treatments, complementary and alternative treatment modalities, such as herbal medicine, have been thought to relieve pain, reduce swelling, and help the body restore damaged tissues [22]. Traditional Korean medications usually contain many compounds that act on multiple targets [23]. The combination of multiple drugs is thought to maximize the therapeutic efficacy by facilitating synergistic actions and preventing potential adverse events (AEs). *Dangguixu-san* (DS), which is composed of *Angelicae gigantis radix*, *Paeoniae radix rubra*, *Linderae radix*, *Cyperi rhizoma*, *Sappan lignum*, *Carthami flos*, *Persicae semen*, *Cinnamomum cassia*, and *Glycyrrhizae radix*, promotes blood circulation and relieves blood stasis; therefore, it is the most frequently prescribed herbal formula for the treatment of traumatic ecchymosis and pain [24] and is recommended for the treatment of ankle sprain [25]. This formula is also known as *Dangkwisoo-san* in Korean and *Tokishusan* in Japanese [26, 27].

Acupuncture is one of the more commonly used therapeutic modalities for painful conditions in complementary and alternative medicine, including Korean medicine [28]. A survey reported that 76% of responding American physicians used acupuncture for ankle sprain, and 90% of them considered it to be somewhat effective [29]. In 2009, approximately 2.8 million Korean individuals were diagnosed with an ankle injury, which was the fifth most common reason for visits to Korean medicine clinics. Of these, 1.2 million individuals sought acupuncture treatment [30]. Considering that DS is mainly used with acupuncture in clinical situations, the present study will use acupuncture as the basic treatment.

Although DS is used for the treatment of ankle sprain in Korean medicine, evidence regarding its efficacy is insufficient. Therefore, we designed a randomized, double-blinded, placebo-controlled, parallel-arm clinical trial for investigating the efficacy and safety of DS for the treatment of ankle sprain. The results of this study are expected to provide evidence regarding the usefulness of DS for the treatment of ankle sprain.

## Method/design

### Objective

The objective of this study is to compare the efficacy of DS treatment combined with acupuncture with that of placebo combined with acupuncture for pain reduction in patients with acute lateral ankle sprain (ALAS) in order to investigate the efficacy of DS for the treatment of ankle sprain.

### Hypothesis

Our null hypothesis is that the pain control effects of DS are not superior to those of placebo in patients with ALAS.

### Study design

The present study design is in accordance with the Standard Protocol Items: Recommendations for Interventional Trials (SPIRIT) and Consolidated Standards Of Reporting Trials (CONSORT) 2010 guidelines [31, 32] (see Additional file 1). The study is a randomized, double-blinded, placebo-controlled, parallel-arm, single-center (Semyung University Korean Medicine Hospital in Chungju, Republic of Korea) clinical trial with a 1:1 allocation ratio. A total of 48 participants who meet the inclusion and exclusion criteria will be randomly allocated to a DS (*n* = 24) or a placebo (*n* = 24) group. Patients in both groups will receive acupuncture treatment once a day for 5 days a week (excluding Saturday and Sunday) and the trial medication (DS/placebo capsule) three times a day for seven consecutive days. The primary outcome measure will be pain relief evaluated using a Visual Analog Scale (VAS). The secondary outcome measures will be Foot and Ankle Outcome Scores (FAOS), edema, European Quality of Life Five-Dimension-Five-Level Scale (EQ-5D-5 L) scores, and the number of recurrent ankle sprains. VAS, FAOS, edema, and EQ-5D-5 L scores will be assessed before, at the end of, and at 4 weeks after treatment completion. EQ-5D-5 L scores will be additionally recorded at 26 weeks after treatment completion. The number of recurrent ankle sprains will be recorded at 4, 8, 12, and 26 weeks after treatment completion.

This study protocol complies with the principles of the Declaration of Helsinki and Korean Good Clinical Practice guidelines and has been approved by the Ministry of Food and Drug Safety (registration number, 20160318110). The trial has been registered at cris.nih.go.kr (registration number, KCT 0002374). The study design is summarized in Table 1 and Fig. 1.

**Table 1 Tab1:** Treatment schedule and outcome measures

	Study period										
	Enrollment	Allocation	Post allocation								Close-out
Timepoint	Screening		Visit1	Visit2	Visit3	Visit4	Visit5	Visit6	Visit7	Visit8	Visit9
	Week		1					5	8	13	27
Enrollment											
Informed consent	X										
Sociodemographic profile	X										
Medical history	X										
Vital signs	X	X	X	X	X	X	X	X			
Inclusion/exclusion criteria	X										
Allocation		X									
Clinical laboratory tests	X						X				
Interventions											
Acupuncture treatment			X	X	X	X	X				
Trial medication prescription			X								
Assessments											
Change of medical history			X	X	X	X	X	X	X	X	X
Safety assessment			X	X	X	X	X	X			
Visual Analog Scale of pain			X				X	X			
Foot and Ankle Outcome Score			X				X	X			
Edema of ankle sprain			X				X	X			
European Quality of Life 5-Dimension-5-Level Scale			X				X	X			X
Number of recurrent ankle injuries								X	X	X	X

**Fig. 1 Fig1:**
[figure not shown]
Study design flow chart

### Participant recruitment

Participants will be recruited at Semyung University Korean Medicine Hospital in Chungju, Republic of Korea. The study will be advertised through local newspapers, the Internet, and posters in communities and hospitals. Participants will be provided with an explanation about the study by the clinical research coordinator (CRC) and will be requested to voluntarily sign an informed consent before participation. The CRC will continuously monitor the medical condition of the enrolled participants to ensure adherence to the intervention protocols.

### Inclusion criteria

Patients aged older than 19 years who have sustained a grade I or grade II ALAS within 72 h before enrollment and are willing to voluntarily sign an informed consent form will be considered for enrollment. A grade I ankle sprain will be diagnosed when there is no loss of function or ligament laxity (*i.e.*, negative anterior drawer and talar tilt test results), little or no hemorrhaging, no point tenderness, decreased total ankle motion by ≤ 5°, and a swelling of ≤ 0.5 cm. Patients with some loss of function, positive anterior drawer test findings (indicating anterior talofibular ligament involvement), negative talar tilt test findings (indicating no calcaneofibular ligament involvement), hemorrhaging, point tenderness, decreased total ankle motion by > 5° but < 10°, and a swelling of > 0.5 cm but < 2.0 cm will be diagnosed with grade II ALAS [33].

### Exclusion criteria

Subjects with a poor general condition and those who are not fit for acupuncture or DS treatment will be excluded. Other exclusion criteria are as follows: fracture confirmed on x-rays or grade III ankle sprain (which will be defined as the near total loss of function, positive anterior drawer and talar tilt test findings, hemorrhaging, extreme point tenderness, decreased total ankle motion by > 10°, and a swelling of > 2.0 cm) [33]; a history of fracture in the same ankle during the previous year; serious disease conditions (*e.g.*, cancer, kidney, liver, and central nervous system diseases, dementia, and blood clotting abnormalities such as hemophilia); motor or sensory disturbance due to nervous system disorders in the same leg; pregnancy or breastfeeding; medication with drugs such as nonsteroidal anti-inflammatory drugs (NSAIDs), pain relievers, or steroids for pain relief from the time of trauma to participation in the clinical trial (excluding the use of adherent inflammatory pain relievers on the day of screening); impaired hepatic (alanine aminotransferase level, ≥ 80 IU/L) or renal (creatinine level, ≥ 2 mg/dL) function; ineligibility for participation in the trial because of a history of gastrointestinal diseases that might affect the absorption of the trial medication, as judged by the principal investigator (PI); genetic conditions such as galactose intolerance, Lapp lactase deficiency, and glucose-galactose malabsorption; a history of hypersensitivity to the components of the trial medication; and participation in other clinical trials within 4 weeks of screening for the present study or concurrent participation in other clinical trials.

### Ethical considerations

This study has been approved by the Institutional Review Board (IRB) of Semyung University Korean Medicine Hospital in Chungju. The purpose and potential risks of this clinical trial will be fully explained to the participants and their families. All participants will be asked to provide written informed consent before participation.

### Randomization and blinding

After the acquisition of written informed consent and completion of baseline measurements, the 48 enrolled participants will be assigned serial numbers generated using a randomization tool (http://www.randomization.com) and randomly allocated to one of the two study groups (*n* = 24 each). The serial number codes will be inserted into opaque envelopes that will be sealed and stored in a double-locked cabinet.

Blinding will be achieved by randomized labeling and prepackaging of DS and placebo capsules, which will be identical in appearance, taste, and smell. The DS and placebo capsules provided by the pharmaceutical company will be labeled with numbers in accordance with the randomization schedule. Investigators will administer these medications in accordance with the randomization number. Randomization and uncovering will be performed by a third-party team of statisticians. Thus, participants, investigators, and outcome assessors will remain blinded to treatment allocation until study completion.

### Implementation

The CRC will generate the allocation sequence, enroll participants, and assign participants to the intervention groups.

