### Quality assurance

This protocol has been reviewed and revised several times by experts on acupuncture, herbal medicine, orthopedics, statistics, and methodology. Before the trial, all researchers will be requested to attend a series of training sessions, which will ensure that the personnel involved fully understand the trial protocol and standard operating procedures (SOPs) that will be employed during the study. The Data Monitoring Committee will be composed of the PI and CRC. The clinical trial will be monitored by a clinical research associate (CRA), who will check all documents related to the clinical trial, including Case Report Forms (CRFs) and SOPs, and ensure that the clinical trial is conducted in accordance with the prescribed protocols and SOPs. Monitoring will be conducted independent of the PI. In the event that the protocol described herein is revised, the revisions will require approval from the Ministry of Food and Drug Safety and the IRB of Semyung University Korean Medicine Hospital in Chungju.

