### Confidentiality and data management

Identification records of the participants will be kept confidential until publication of the results of the study. All documents related to the trial, including CRFs, will be recorded and labeled with participant identification codes and will not show the name of the participant. These serial number codes will be stored in sealed, opaque envelopes and kept in a double-locked cabinet. All participant data will be recorded in Excel files by the CRC. In additionally, raw data (CRFs) will be stored in a cabinet until the end of the study. Written informed consent for the publication of individual details and accompanying images will be obtained from the participants.

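### The protocol names two different parties as the one who randomises; if the Implementation section is followed, allocation is not concealed from the coordinator who enrols participants

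*Protocol article*

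**What the plan says.** Under Randomization and blinding, serial numbers come from an online randomisation tool and storage is described as follows: "The serial number codes will be inserted into opaque envelopes that will be sealed and stored in a double-locked cabinet". The capsules are the blinding device: "Blinding will be achieved by randomized labeling and prepackaging of DS and placebo capsules, which will be identical in appearance, taste, and smell". Labelling follows the list: "The DS and placebo capsules provided by the pharmaceutical company will be labeled with numbers in accordance with the randomization schedule". The section then names who is in charge: "Randomization and uncovering will be performed by a third-party team of statisticians". From this it concludes: "Thus, participants, investigators, and outcome assessors will remain blinded to treatment allocation until study completion".

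The next section, Implementation, is one sentence: "The CRC will generate the allocation sequence, enroll participants, and assign participants to the intervention groups".

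The CRC has other duties. Under Participant recruitment, the CRC explains the study to candidates and follows enrolled participants' condition so that they keep to the interventions. Under Incidence of adverse events, the CRC documents each event, including severity and possible relation to treatment, and reports it to the principal investigator (PI) and the IRB. Under Confidentiality and data management: "All participant data will be recorded in Excel files by the CRC". Trial status says that the trial is ongoing.

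**The concern.** Allocation concealment requires that whoever decides whether a candidate enters cannot know the next assignment. The usual way to secure this is to separate the party who makes the list from the party who enrols. One section of the article makes that separation and the next undoes it.

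Two things are at stake. The first is selection at entry: a person who knows the next assignment can, even without intent, hurry, delay or discourage a candidate. With 24 per group, a few such decisions could shift the baseline mix, and adjusting for measured covariates would not repair imbalance in unmeasured ones. The second is information bias in what the CRC handles after entry. Adverse-event causality is a judgement, and adherence monitoring and data entry also leave room for discretion.

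This is not detail that a condensed article leaves to the full protocol. Both statements are in the article, and they disagree.

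**Working it through.** No arithmetic from the plan needs reproducing. The check is a comparison of the two sections, followed by the consequences of each.

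**Step 1: who does what.**

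- Generating the sequence: the CRC (Implementation). Randomization and blinding gives randomisation as a whole to the third-party statisticians.
- Assigning participants: the CRC (Implementation); again part of the third party's task under Randomization and blinding.
- Enrolling: the CRC (Implementation). The other section does not contradict this.
- Breaking the code: the third-party statisticians. Implementation is silent.

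**Step 2: can both statements be true?** Two reconciling readings can be tried.

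- The third party oversees and the CRC carries out. If the CRC both generates the sequence and assigns participants, nothing of substance in randomisation is left for the third party except breaking the code.
- The CRC merely hands out the next number. That would explain the word assign, but not the statement that the CRC generates the sequence.

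Neither reading leaves both sentences standing as written.

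**Step 3: if Implementation is followed.** The list's author is also the enroller. Envelopes and a locked cabinet protect a list from people who have not seen it, and the author has. Pre-numbered packs do not help either, because they are numbered to that same list. The number of allocations exposed is at most 24 + 24 = 48, that is, all of them. Reaching that maximum requires that the CRC keeps or recalls the list and that it identifies treatment. The article states neither. With group codes only, the CRC would know which participants share a group but not which group receives the herbal product. Concealment is still impaired, but the knowledge is partial.

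**Step 4: effect on blinding, role by role.**

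- Participants: blinded by identical capsules, whoever made the list. They mark the pain VAS, the primary outcome, themselves.
- Treating physicians: blinded by the same capsules, provided that the list is not disclosed to them.
- CRC: fully or partly unblinded, depending on what the list shows. The sentence on who stays blinded names participants, investigators and outcome assessors; it does not name the CRC.

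**Step 5: if Randomization and blinding is followed.** The Implementation sentence is then misworded, and concealment may be intact.

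**Step 6: size of the bias.** It cannot be derived. The Sample size estimation section sets 24 per group on feasibility and gives no SD, effect size or power. Any figure in millimetres of VAS would be invented.

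**The case against.** The best defence is that the third-party arrangement is the real one and that the Implementation sentence is loose drafting. The envelopes, the manufacturer's labelling to a schedule and the explicit blinding conclusion all fit a third-party process. This is plausible, and it is why the loss of concealment is stated here only as conditional. It does not remove the contradiction: site staff could follow either section, and a reader cannot tell which applied.

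Some stronger inferences are tempting, but the document does not support them.

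- **That the trial is no longer double-blind.** Participant and physician blinding depends on the capsules, and nowhere is the CRC called an outcome assessor.
- **That the CRC decides who is dropped from the analysis.** Statistical analysis lists the dropout criteria and names only the PI or IRB as ending participation. It gives the CRC no such decision.
- **That the CRC alone judges causality or controls the data unchecked.** The CRC records events and reports them to the PI and IRB. Under Quality assurance, a clinical research associate checks trial documents, including case report forms, independently of the PI. This check bears on data distortion but cannot restore concealment.
- **That the monitoring committee exposes the allocation.** Quality assurance says: "The Data Monitoring Committee will be composed of the PI and CRC". It does not say that the committee sees unblinded data, and no interim analyses are planned. Its membership is a separate matter from who makes the list.

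**Conclusion.** The point stands as an internal contradiction that must be corrected. Two adjacent sections give randomisation to different parties, and following the second as written defeats concealment from the person who enrols.

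In size, between none and all 48 allocations are affected, depending on which section describes practice and on what the list shows. Beyond that, the CRC's adverse-event, adherence and data-entry work may be unblinded. Blinding of participants and physicians is not shown to be lost.

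The conclusion assumes that the CRC is the same person, or a team sharing access to the list, in every section where the role appears; the article says nothing to the contrary. It does not depend on any assumed effect or variance.

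**What to change.** First, because enrolment is under way, document who ran the randomisation tool, who has held the list and key since then, and whether the list shows treatment names or codes.

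Then amend the Implementation section to agree with Randomization and blinding, for example: *The third-party statistical team generates the allocation sequence, holds the list and code key, and supplies the list only for capsule labelling. The CRC enrols participants and issues the next pre-numbered pack in strict order, and has no access to the list until database lock.*

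If the record shows that the third party did this from the start, the amendment is only a correction of wording. If the CRC generated or held the list, rewording is not enough. The third-party team should regenerate the sequence for the remaining participants, and the trial report should state that allocation was not concealed from the enrolling coordinator for those already entered.

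The third-party team and the numbered packs are already named in the article, so the correction adds no new party. The amendment needs approval from the Ministry of Food and Drug Safety and the IRB, as Quality assurance requires for any revision. If the sequence is regenerated, the unused packs must also be relabelled or renumbered to match it.
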